# MENOS4 trial: a multicentre randomised controlled trial (RCT) of a breast care nurse delivered cognitive behavioural therapy (CBT) intervention to reduce the impact of hot flushes in women with breast cancer: Study Protocol

**DOI:** 10.1186/s12905-018-0550-z

**Published:** 2018-05-08

**Keywords:** Breast cancer, Menopause, Hot flushes, Night sweats, CBT, Training, Nurses, Normalisation process theory

## Abstract

**Background:**

Women who have been treated for breast cancer may identify vasomotor symptoms, such as hot flushes and night sweats (HFNS), as a serious problem. HFNS are unpleasant to experience and can have a significant impact on daily life, potentially leading to reduced adherence to life saving adjuvant hormonal therapy. It is known that Cognitive Behavioural Therapy (CBT) is effective for the alleviation of hot flushes in both well women and women who have had breast cancer. Most women with breast cancer will see a breast care nurse and there is evidence that nurses can be trained to deliver psychological treatments to a satisfactory level, whilst also maintaining treatment fidelity. The research team will assess whether breast care nurses can effectively deliver a CBT intervention to alleviate hot flushes in women with breast cancer.

**Methods:**

This study is a multi-centre phase III individually randomised controlled trial of group CBT versus usual care to reduce the impact of hot flushes in women with breast cancer. 120–160 women with primary breast cancer experiencing seven or more problematic HFNS a week will be randomised to receive either treatment as usual (TAU) or participation in the group CBT intervention plus TAU (CBT Group).

A process evaluation using May’s Normalisation Process Theory will be conducted, as well as practical and organisational issues relating to the implementation of the intervention. Fidelity of implementation of the intervention will be conducted by expert assessment. The cost effectiveness of the intervention will also be assessed.

**Discussion:**

There is a need for studies that enable effective interventions to be implemented in practice. There is good evidence that CBT is helpful for women with breast cancer who experience HFNS, yet it is not widely available. It is not yet known whether the intervention can be effectively delivered by breast care nurses or implemented in practice. This study will provide information on both whether the intervention can effectively help women with hot flushes and whether and how it can be translated into routine clinical practice.

**Trial registration:**

ISRCTN 12824632. Registered 25–01-2017.

**Electronic supplementary material:**

The online version of this article (10.1186/s12905-018-0550-z) contains supplementary material, which is available to authorized users.

## Background

Hot flushes, also known as hot flashes, and night sweats (HFNS) are experienced by up to 70% of women after treatment for breast cancer [29]. HFNS are troublesome for many women, having a significant impact on daily life and sleep quality, with important social consequences affecting employment, personal relationships and quality of life [17]. With natural menopause, HFNS gradually decrease in number and intensity over the post-menopausal years. With breast cancer, HFNS can be more extreme and persistent: experienced by 34% of women more than five years after diagnosis and by 50% of women more than five years from menopause [16]. This is due in part to treatments for breast cancer, which reduce or interfere with the action of oestrogen in the body. Chemotherapy may precipitate an early menopause [30] and tamoxifen and other hormonal treatments cause or exacerbate HFNS [32]. Adjuvant hormone therapies may be used sequentially for a minimum of five years and now up to ten years post diagnosis. The majority of women do not complete the recommended five years of adjuvant hormone therapy, which may be partly due to adverse side effects, such as HFNS, resulting in a 30% increased breast cancer mortality [25, 28].

The most effective treatment for HFNS is hormone replacement therapy, which is contraindicated in ER+ breast cancer [31]. While there are other medications available, such as selective serotonin re-uptake inhibitors (SSRIs) and clonidine, they have unpleasant side effects, and non-medical alternatives tend to lack efficacy [7]. Furthermore, many women prefer not to take medication after cancer, but instead favour self-management of menopausal HFNS [34]. Surveys carried out by the National Cancer Research Institute (NCRI) breast symptoms working party showed that there are no consistent standard care pathways for people with HFNS and that very few women are offered anything in the way of care or management of this problem [15].

There is evidence that a structured cognitive behavioural therapy (CBT), focusing on key elements of the experience of hot flushes and night sweats, delivered in group format, is effective for the alleviation of HFNS in both women with and without breast cancer [1, 12, 26]. In line with the Medical Research Council’s guidance on developing and evaluating complex interventions [11] the theoretical basis and the role of moderators and mediators of the outcomes of CBT have been examined in previous studies. Hunter and Mann [22] developed a theoretical model of HFNS that draws upon symptom perception, self-regulation and cognitive behavioural theories to explain women’s cognitive appraisal and behavioural reactions to symptoms. The model was tested using structural equation modelling [21] and an examination of mediators in MENOS trials [10]. The results clearly suggest that problem rating of HFNS (i.e. the impact of HFNS on daily life) is mediated mainly by beliefs about HFNS, and that changes in beliefs, as well as improvements in mood and sleep, predict positive outcomes with CBT.

There may be a need to develop a variety of ways to deliver the CBT intervention, but group sessions, led by a health professional such as the breast care nurse (BCN), provide a cost effective solution, and were positively viewed in the previous MENOS trial [2]. There are also benefits with group CBT, such as improvements in mood and quality of life, which have not been demonstrated with self-help CBT [1]. Although CBT is known to be effective, it is rarely offered within the NHS for women with breast cancer. It is also not known whether this intervention can be effectively delivered by BCNs in the NHS context. Most women with breast cancer will see a BCN and there is evidence to suggest that it is possible to train BCNs to deliver psychological interventions to a satisfactory level and fidelity [24]. This study will therefore test whether breast care nurses can be trained to deliver CBT in an NHS context to effectively manage HFNS in women who have had breast cancer.

A further consideration is that practical barriers can prevent effective interventions from being delivered in practice, so we will conduct a process evaluation, drawing on May’s Normalisation Process Theory (NPT), [33], to explore potential barriers to implementation. The theory focuses on the dynamic processes that lead to innovations being implemented and integrated into work on an every-day basis. It is therefore a helpful way to assess what happens when multifaceted interventions are introduced into practice. This includes what people’s actions are, collectively and individually, and how and why the desired outcomes are met (or not). The processes that take place when people implement change are described by NPT as coherence, cognitive participation, collective action and reflexive monitoring. The intervention in this trial is an alternative care pathway that includes CBT. The purpose of the process evaluation is to understand the dynamics of the care pathway and identify factors that are important for embedding this intervention into practice. This evaluation will focus on identifying and explaining the extent to which the planned CBT is implemented into practice.

HFNS have been identified as a major physical symptom by the breast cancer research gap analysis [13], requiring research that identifies appropriate interventions to enable women to manage this problem. The research gap analysis also highlights an inadequate translation of research findings into clinical practice and specifically the need to consider how interventions such as CBT can be better integrated to widen access.

## Methods/Design

The study design is a randomised controlled trial (RCT), with a formal process evaluation. The RCT will be a multi-centre phase III individually randomised controlled trial of a BCN-delivered group CBT intervention versus treatment as usual (TAU).

### Study aims and objectives

The primary study aim is to evaluate the effectiveness of group CBT delivered by breast care nurses on reducing the impact of HFNS in women with breast cancer 26 weeks after randomisation.

Secondary aims include outcome and process issues. These are to explore and evaluate:The extent to which there is a reduction of the impact of HFNS nine weeks after randomisation in women with breast cancerThe extent to which there is a reduction of the frequency of hot flushes and night sweats nine and 26 weeks after randomisation in women with breast cancerThe level of fidelity of the CBT when delivered by breast care nursesThe effect of group CBT on quality of life and other symptoms, e.g. sleep, anxietyThe effect on women’s hot flush beliefs and behavioursAn estimate of the cost-effectivenessThe extent to which the planned CBT intervention was implemented into practice, specifically:Exploring how and in what ways the therapy was initially received, how individually and collectively people practically conceptualised and made sense of it (coherence)Assessing the degree of ownership of and participation in the new practice by key individuals (surgeons, managers, BCNs and patients) and teams (cognitive participation)Identifying the individual and teamwork carried out to sanction the new practice (collective action)Exploring the perceived impact of the new practice on staff work and on patient outcomes (reflexive monitoring)

### Study setting

Participants will be recruited from six NHS Hospital Trusts in England and Wales. These centres will be selected from those who express an interest through the NIHR Clinical Research Network (CRN) and will have:Availability of at least two BCNs willing to be trainedAvailable room to deliver the CBT sessionsWritten agreement to participate from the manager

### Participants

120–160 women with primary breast cancer experiencing seven or more problematic HFNS a week will be recruited and randomised to the intervention or usual care.

Inclusion criteria are:Women with primary breast cancer or ductal carcinoma in situ (DCIS)Women who have completed all primary treatment: surgery and/or radiotherapy and/or chemotherapy (may still be receiving adjuvant endocrine therapy or Herceptin)Aged 16 years or olderExperiencing seven or more HFNS/week with an overall rating of 4/10 or above on the Hot Flush Problem Rating ScaleAbility to attend group sessionsSigned informed consent

The exclusion criteria are:Benign breast diseaseMetastatic disease (our patient representatives advised us that the group dynamics could be dominated by issues of recurrence and disease progression instead of focusing on HFNS if people with metastatic disease were included)Current use of other mind-body therapies to help with HFNS, e.g. acupuncture, hypnosis and mindfulness.

There will be no exclusion criterion relating to time since diagnosis as long as participants have problematic HFNS. Women who are taking medication or herbal remedies for HFNS will be asked to continue with these throughout the study.

### Study processes

Due to the pragmatic nature of the study, and to emulate the real world situation of this intervention, potential participants will be identified and recruited as flexibly as possible. Therefore, routes of identifying eligible women will include identification from breast cancer follow up clinics, phone clinics, leaflets and posters in clinics and health and wellbeing events, by the research nurses, who will check eligibility and take consent following GCP guidelines.

### Randomisation

Randomisation will be in cohort groups and stratified by site. A computer-generated randomisation sequence will be created by a statistician at the Clinical Trials Unit, allocating participants in a one-to-one ratio, stratified by site with fixed block size. This process will be repeated for each cohort group so that allocation does not affect the allocation sequence of subsequent cohorts. Following receipt of consent and completed baseline case report forms (CRFs) from 12 to 16 eligible participants at a single site participants will be randomised to either Group CBT or TAU. The research nurse will be sent the allocation results for all the women at one time point and they will inform each participant of their group allocation (CBT or TAU). Each site will aim to run two sequential groups of the intervention of 6–8 women per group (NB. A possible group of five (ten women recruited) was also possible via TMG approval).

### Intervention

Women in the intervention arm will attend weekly group CBT sessions, lasting 90 min each, for six weeks. Sessions will be delivered by BCNs who have been trained by a clinical psychologist. The sessions will follow a structured manual [20], which includes psycho-education and the cognitive behavioural model; stress management; paced breathing; cognitive and behavioural strategies to improve wellbeing and for managing hot flushes; night sweats and sleep; and maintaining changes.

### Training

The BCNs involved in delivering the intervention will be selected by sites and will be trained by a clinical psychologist to deliver the intervention. The nurses will be trained as close as practically possible to delivery of the intervention. Training will take place over two days, with 6 h of training per day and an overnight stay in between. Knowledge and skills will be assessed throughout the training using a variety of methods, including questionnaires and role-plays. A telephone based top-up session will be conducted immediately prior to the first group at each site (within three weeks) in order to refresh the learning.

BCNs will use a manual [20] which contains detailed session content, presentation slides and handouts, and notes for facilitators. This will be sent to BCNs in advance of the training days with tasks to complete in preparation, including a sleep diary and relaxation CD. The training will provide the background theoretical knowledge and practical skills to facilitate group CBT for menopausal symptoms by examining how thinking and behaviour can have a significant impact on women’s experience of HFNS following breast cancer treatment and helping women to develop strategies to manage them. These include understanding negative emotions and HFNS, managing unhelpful thoughts and behaviour, improving sleep and using paced breathing to manage HFNS.

### Supervision

BCNs will receive ongoing supervision of their delivery of group CBT. They will be asked to write down their reflections and any questions/problems after each session they deliver and email it to the clinical psychologist who trained them for supervision. Feedback on these reflections will be made by email, telephone or Skype. They can also refer back to the manual. Data will be collected on the number and length of supervisory sessions.

### Adherence

Adherence to group CBT will be measured by the number of sessions attended and the number of times that a participant reports practising relaxation and paced breathing each week. If participants do not attend a session, the BCN will contact the participant by telephone to ascertain the problem of attendance, and will discuss the appropriate solution with the participant e.g. a telephone session. Alternatively, the session is recorded as did not attend. Telephone sessions will be kept to a minimum, and only arranged if exceptional circumstances do not allow the patient to attend the face-to-face session.

### Fidelity

All group sessions will be audio recorded (with consent), and 17% will be randomly selected (with a computer-generated random number sequence), ensuring two sessions per site are selected. An independent psychologist (i.e. who has not been involved in BCN training), experienced in CBT for HFNS, will rate them for adherence to the treatment manual.

### Treatment as usual arm

It is expected that TAU will be different at each site as there is no current standard of care. Since randomisation will be stratified by site this does not pose a problem. In some centres, women will be given ad hoc advice about HFNS, normally only if they raise the issue. Data collected from a UK survey suggests that only 29% women were asked if they were experiencing HFNS, only 2% were referred to a menopause clinic and very few offered any kind of relaxation or behavioural intervention [15].

In addition to standard NHS care, participants randomised to the TAU arm will be offered a version of self-help CBT following the 26-week assessment. This involves giving women a booklet and CD that includes the same information as group CBT sessions, as well as a one-to-one face-to-face meeting with a trained BCN to discuss the key elements of the booklet. This will be followed up by two telephone calls to discuss progress, encourage use of the booklet and homework and to address any problems. Offering self-help CBT will be used as a strategy to increase adherence to the study.

### Outcome measures

Outcome measures will be completed at baseline, week nine and week 26. Baseline demographic and clinical information, including use of current therapies, will be collected and input on the database. A team from the Clinical Informatics Research Unit at the University of Southampton will develop the trial database. The infrastructure will be provided by ALEA.

#### Hot flushes and night sweats assessment

The primary study outcome will be measured using the Hot Flushes and Night Sweats (HFNS) Problem Rating Scale [18]. This measures the extent to which hot flushes and night sweats are problematic, distressing and interfere with daily life. Three items are rated on a 10-point scale – higher scores are indicative of greater bother/impact on daily life. A change of 2 points on this scale is considered clinically relevant [1, 26]. This scale also assesses HFNS frequency asking women to estimate how many HFNS they have had in the past week. A three day diary will be collected at baseline to validate the accuracy of the estimate.

The Short Form Hot Flush Beliefs and Behaviours Scale (HFBBS) is a 16-item scale that includes items about beliefs and behaviours about hot flushes [19]. Subscales include: (i) beliefs about HF in social context (e.g. everyone is looking at me), (ii) beliefs about coping/control of hot flushes (e.g. when I have a HF I think they will never end), and (iii) beliefs about night sweats and sleep (e.g. if I have NS I’ll never get back to sleep). HFNS Behaviours include (i) positive coping behaviour, e.g. accepting HFNS, using breathing and calming responses; (ii) avoidance behaviour.

The Hot Flash Related Daily Interference Scale (HFRDIS) [9] measures the impact of hot flushes on a variety of domains including work, social, and leisure activities on a scale from 0 to 10.

#### Quality of life

QoL will be assessed using the EQ-5D-5 L and the FACT-B [4]. FACT -B is a widely used and well-validated 37-item questionnaire designed for use in breast cancer. Five sub-scales assess physical, social, emotional and functional well-being, as well as concerns specific to women with breast cancer. The endocrine subscale (ES) [14] includes 19 items related to hormone treatment.

#### Anxiety and depression

The Generalised Anxiety Disorder Questionnaire (GAD-7) is a self-administered patient questionnaire consisting of seven items (e.g. feeling nervous, restlessness) used as a severity measure for generalised anxiety disorder [35].

The Patient Health Questionnaire-9 (PHQ-9) is a measure of depressive mood. It is used to examine the severity of depression and response to treatment. It is self-administered and patients are asked how often they have been bothered by nine problems (e.g. trouble concentrating and poor appetite) over the previous two weeks [23].

#### Sleep

The Pittsburgh Sleep Quality Index (PSQI) is a self-rated questionnaire that assesses sleep quality and disturbances from 19 individual items, including sleep quality, sleep latency, sleep duration, habitual sleep efficiency, sleep disturbance, sleep medication use and daytime dysfunction (Bussye et al. [6]). These are analysed in seven component scores with the sum of scores yielding one total score. This has been validated for use in women with breast cancer [8].

#### Health economics assessment

The economic analysis will estimate the costs of providing the CBT intervention, and the cost consequences of the intervention for NHS services and for costs borne by patients. However, an economic evaluation will be conducted only if the intervention proves to be effective, as defined by a two-point improvement in the HFNS. The cost of the intervention will be reported regardless of its effectiveness. If effective, cost effectiveness will be expressed in cost per unit change in HFNS and per QALY, based on the incremental differences between arms. The identification and collection of costs will be undertaken using the following methods:

1) NHS

Data on the use of medication, primary care visits, and out-patient visits will be collected using a resource use questionnaire. The cost of the intervention will be based on nurse logs to record staff training cost, and time to deliver the intervention. This information will be used for sensitivity analysis from a societal perspective. We will use an adapted form of the client service receipt inventory (CSRI), Beecham & Knapp, [3].

2) Women

We will estimate out-of-pocket spending such as herbal remedies, acupuncture or alternative therapies and time off work due to hot flushes. Collection of such information from each participant will be through a resource use questionnaire at 9 and 26 weeks. QoL will be measured by EQ-5D-5 L and will be collected at baseline, 3, 6, 9 and 26 weeks.

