### Analysis

#### Sample size calculation

A difference of two points or more in the HFNS Problem Rating Scale is regarded as clinically relevant. In order to detect a two-point difference (standard deviation 2.4; standardised effect size 0.8, [26] in mean HFNS problem rating for the comparison of CBT to TAU, 90% power would require 64 participants in total (32 per randomised arm), assuming 2-sided significance level of 0.05. Allowing for an inflation factor of 1.49 (intraclass correlation of 0.07 with 8 participants per group, (Wampold and Brown [36]) to adjust for expected clustering of outcomes within groups, gives a minimum sample size of 96, which increases to 120 allowing for 20% loss to follow-up. A sample size of 120 will also allow each site to run two groups to ensure that a comprehensive process evaluation can be conducted. If each site recruits the minimum number of six people per group, then 120 participants in total will be achieved. If they recruit the maximum of eight per group (allowing up to 160 participants in total) this will provide greater power for the analyses of secondary outcomes.

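### The cost-effectiveness analysis is conditional on an HFNS improvement equal to the design difference, so if the true effect is 2.0 points it is withheld about half the time

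*Protocol article*

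**What the plan says.** All references are to the protocol article.

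- **Health economics assessment** sets the condition: "an economic evaluation will be conducted only if the intervention proves to be effective, as defined by a two-point improvement in the HFNS". One item is exempt: "The cost of the intervention will be reported regardless of its effectiveness". The ratios depend on passing: "If effective, cost effectiveness will be expressed in cost per unit change in HFNS and per QALY, based on the incremental differences between arms".
- **Abstract, Methods** states the aim with no condition: "The cost effectiveness of the intervention will also be assessed". **Study aims and objectives** likewise lists an estimate of cost-effectiveness among the secondary aims, unqualified.
- **Sample size calculation** uses the same two points as the design difference: "In order to detect a two-point difference", with "standard deviation 2.4; standardised effect size 0.8". It continues "90% power would require 64 participants in total (32 per randomised arm"), "assuming 2-sided significance level of 0.05". An inflation factor of 1.49 (ICC 0.07, eight per group) takes this to 96, and 20% loss takes it to 120.
- **Primary and secondary analyses** judges the primary outcome by a linear mixed model comparing the arms. The economic condition does not refer to that test.

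**The concern.** A threshold on an estimate, set at the value the trial assumes to be true, is passed or failed by chance about equally often when the assumption is right. Here it decides whether a stated secondary aim is addressed. An observed difference of 1.9 does not show that the true effect is below 2, yet it would stop the analysis.

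The condition also departs from the primary test: a clearly significant result can fall short of two points. It is a poor screen for cost per QALY, which depends on EQ-5D and costs rather than on HFNS rating. And Health economics analysis plans bootstrapping and acceptability curves to display uncertainty, which a cut-off on a point estimate sets aside before the analysis starts.

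Finally, the condition does not say which contrast, which time point (outcomes are taken at weeks 9 and 26), or whether the estimate or a confidence limit must reach two points.

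**Working it through.** **Inputs** (Sample size calculation; 1:1 allocation from Randomisation): difference 2, SD 2.4, two-sided alpha 0.05, power 90%, ICC 0.07, eight per group, 20% loss.

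**1. Reproducing the plan's sample size.**
- A t-based calculation with effect size 2/2.4 = 0.833 gives 31.25, so 32 per arm and 64 in total.
- Inflation: 1 + (8 - 1) x 0.07 = 1.49; 64 x 1.49 = 95.4, rounded up to 96.
- Loss to follow-up: 96/0.80 = 120.

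The stated 64, 96 and 120 are reproduced.

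**2. Standard error of the between-arm difference, 96 analysed (48 per arm).**
- Protocol basis, inflation in both arms: SE = 2.4 x sqrt(2 x 1.49/48) = 0.598. Differences of at least 1.96 x 0.598 = 1.17 are significant.
- Clustering in the CBT arm only: SE = 2.4 x sqrt((1 + (m - 1) x 0.07)/48 + 1/48). This is 0.547 for m = 8 women analysed per group and 0.521 for m = 4.8 (six per group less 20%).

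**3. Chance of meeting the condition, read as the between-arm point estimate.** For true difference D:
- P(condition met) = 1 - Phi((2 - D)/SE)
- P(significant) = 1 - Phi(1.96 - D/SE)

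At D = 2 the first is 1 - Phi(0) = 0.50 for every SE. A simulation with clustering in the CBT arm gave 0.499. With SE = 0.598:

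| True difference | Condition met | Significant | Significant, condition not met |
|---|---|---|---|
| 1.5 | 0.20 | 0.71 | 0.51 |
| 1.75 | 0.34 | 0.83 | 0.50 |
| 2.0 | 0.50 | 0.92 | 0.42 |
| 2.25 | 0.66 | 0.96 | 0.30 |
| 2.5 | 0.80 | 0.99 | 0.19 |
| 3.0 | 0.95 | >0.99 | 0.05 |

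With clustering in the CBT arm only (SE 0.521-0.547), P(significant) at D = 2 is 0.955-0.97, so the last column becomes 45-47%. At D = 1.5, 17-18% meet the condition and 78-82% are significant.

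**4. Does a larger sample help?** With 160 recruited and 128 analysed, SE = 2.4 x sqrt(2 x 1.49/64) = 0.518. P(condition met) at D = 2 is still 0.50, while P(significant) rises to 0.97, so the mismatch grows.

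**5. Selection of the reported ratio.** At D = 2, the mean observed difference among trials that pass is 2 + 0.798 x SE: 2.42 for SE 0.521 and 2.48 for SE 0.598. Cost per unit HFNS would thus be reported only with a denominator that is too large on average.

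**6. Other basis.** If proving effectiveness meant a lower 95% limit of at least 2, P(condition met) at D = 2 would be 0.025.

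**The case against.** The best defence is that the rule is prespecified and its threshold is the article's stated clinically relevant difference, so it is not arbitrary. Leaving out cost-effectiveness work when benefit is below clinical relevance is a possible resource decision, and one-line aims in a condensed article may be read as qualified by the detailed section. The 50% arises for any threshold placed at the assumed truth and does not say how likely that truth is: at true differences of 2.5 or 3.0 the condition is usually met.

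This limits the size of the problem but does not remove it. The true value at issue is the one the trial was designed around, the analysis saved would use data already planned, and the detailed section still leaves the unconditional aim unanswered in many plausible trials.

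A reader might infer several stronger points that the article does not support:

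- *The EQ-5D and resource-use data would go unused.* EQ-5D-5L is also listed under Quality of life, and secondary outcomes are to be modelled like the primary. Intervention cost is reported regardless, and the opening of Health economics assessment can be read as keeping a description of NHS and patient costs outside the condition.
- *A significant 1.5-point benefit would be called ineffective.* The two-point definition governs only the economic evaluation; the primary result rests on the mixed model.
- *Every reported ratio would be biased by its denominator.* That applies directly to cost per unit HFNS. Any selection of cost per QALY is indirect and cannot be quantified from the article.
- *Regression to the mean in the CBT arm could trigger the analysis.* This needs a within-arm reading, which is less natural because the sample size section and the ratios both concern differences between arms. No figure in the article supports it.

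**Conclusion.** The point holds as a should-fix. The incremental economic evaluation (cost per unit HFNS and per QALY) depends on an estimate reaching the design difference, although the aim is stated without condition. If the true difference is 2.0, it is withheld in 50% of trials, and in about 42% (protocol SE) or 45-47% (clustering in the CBT arm only) despite a significant primary result.

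The 50% needs only an unbiased, symmetric estimator and the between-arm point-estimate reading; it does not depend on SD, sample size, ICC or dropout. The other percentages rest on SD 2.4, 96 analysed and the stated clustering. They ignore the planned baseline adjustment, for which the article gives no correlation. A smaller SE would raise P(significant) and so bring the 42% nearer to 50%.

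The analysis would be withheld, not made impossible. The primary estimate, its type I error and its power are untouched.

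**What to change.** In Health economics assessment, delete the condition and write, for example: *The within-trial economic evaluation (cost per unit HFNS difference and cost per QALY, with bootstrap intervals and cost-effectiveness acceptability curves) will be done and reported whatever the primary result. The HFNS effect is the adjusted between-arm difference at 26 weeks.*

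This agrees with the abstract and the secondary aims, settles the contrast and time point, and removes the selection of the cost-per-HFNS ratio. Tying the condition to a significant primary test instead would be only a partial remedy: at a true difference of 2.0 the evaluation would run in about 92% of trials, but reporting would still depend on the result.

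The cost is some extra health-economist analysis time. No new data are needed, because EQ-5D and resource-use collection is already planned. The change should be made before outcome data are analysed.
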